## 6.2 Preparation/Handling/Storage/Accountability

### 6.2.1 Acquisition and accountability

### 6.2.2 Formulation, Appearance, Packaging, and Labeling

### 6.2.3 Product Storage and Stability

### 6.2.4 Preparation

## 6.3 Measures to Minimize Bias: Randomization and Blinding

The study will be double blind, neither investigators or subjects will know whether subjects are receiving dronabinol or placebo during either dosing period. To protect this blinding study team personnel will not be aware of the results of the urinary toxicology done after randomization. Study team personnel and subjects will be aware that subjects will take dronabinol 5 mg capsules or placebo, but they will not know which dosing period involves dronabinol or placebo.

Study group assignment procedures, and rationale for intervention’s dose, frequency and administration.

Subjects meeting all eligibility criteria will be randomized to dronabinol or placebo for 8 weeks.  We will randomize in a 1:1 ratio, via central, computer-generated randomization done by the pharmacy, stratified by history of prior cannabis use (yes or no) and presence of neuropathic pain (yes or no). To minimize bias in treatment group allocation, the data manager will store the allocation sequence using a password-protected file and has no contact with study participants. We will use urn randomization to minimize risks of imbalance in treatment allocation.

Neuropathic pain will be defined by Leeds Assessment of Neuropathic Signs and Symptoms (LANSS) (score >12). Past-year cannabis use will be defined by self-report of any cannabinoid use (medical, illicit, or cannabidiol containing (CBD) products) in the past year. Based on our prior experience as well as the experience of others, we expect 50% to have neuropathic pain and 50% to have past-year cannabis use after excluding frequent cannabis users.

Capsules of generic dronabinol will be over-encapsulated with methylcellulose filler in between the capsules and placebo will be formulated with matching cellulose capsules filled with methylcellulose. Matching labels for dronabinol and placebo bottles will be provided.

Encapsulated Dronabinol Capsules

For blinding, one intact active dronabinol capsule will be placed in a capsule shell, back filled with sufficient quantity of microcrystalline cellulose, and closed. The capsules are visually inspected and packed into Polypropylene bottles .

Placebo for Encapsulated Dronabinol Capsules

Matching placebo will be compounded, using a matching empty capsule filled with sufficient quantity of microcrystalline cellulose. The capsules are visually inspected and packed into Polypropylene bottles.

Unblinding may be done in the case of some serious adverse events (SAEs), defined as those which result in death, are life-threatening, require inpatient hospitalization or prolongation of existing hospitalization, result in significant disability or incapacity, or result in congenital anomaly or birth defect, [name] will be notified and if the event is determined to be possibly related to dronabinol it will be discontinued.  Dronabinol will not be discontinued for SAEs determined to be unrelated to dronabinol, such as pain crisis. In the event that a participant withdraws from the study or discontinues dronabinol due to a SAE, the participant will be unblinded.

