# 7 Study Intervention Discontinuation and Participant Discontinuation/Withdrawal

## 7.1 Discontinuation of Study Intervention

For serious adverse events (SAEs), defined as those which result in death, are life-threatening, require inpatient hospitalization or prolongation of existing hospitalization, result in significant disability or incapacity, or result in congenital anomaly or birth defect, [name] will be notified and if the event is determined to be possibly related to dronabinol it will be discontinued.  Dronabinol will not be discontinued for SAEs determined to be unrelated to dronabinol, such as pain crisis. In the event that a participant withdraws from the study or discontinues dronabinol due to a SAE, the participant’s ongoing status will be monitored by [name] until: 1) a resolution is reached, i.e., the problem requiring hospitalization has resolved or stabilized with no further changes anticipated; 2) the SAE is determined to be clearly unrelated to study intervention; or 3) the SAE results in death. In cases where a participant discontinues dronabinol for any reason, the Study

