 Coordinator will ask the participant to continue to attend all study visits and complete assessments. Criteria for discontinuation of the randomization condition include 1) pregnancy; 2) current suicidal ideation with plan or intent; 3) suicide attempt; 4) severe anxiety episode, severe depression episode, or psychotic symptoms; 5) severe adverse events probably or definitely related to the randomization condition, as defined above; 6) adverse events that have the potential to cause serious impairment of health, including ischemic or arrhythmic adverse cardiovascular disease events (e.g., myocardial infarction, unstable angina, coronary revascularization, coronary artery disease, unstable arrhythmias, transient ischemic attack, stroke, or congestive heart failure); 7) serious adverse events, defined as those which result in death, are life threatening, require inpatient hospitalization or prolongation of existing hospitalization, result in significant disability or incapacity, or result in congenital anomaly or birth defect; or 8) the request of participants or their treating providers. [name] or the Study Coordinator will be responsible for informing the participant to discontinue the randomization condition and will ask the participant to continue to attend all study visits. Once the randomization condition has been discontinued it will be for the duration of the study.

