## 9.3 Populations for Analyses

Primary analysis of all endpoints will be an intention to treat analysis.  Secondary analysis will be done removing patients who do not complete at least 4 weeks on study as well as any patients whose urine samples show presence of cannabinoid metabolites other than THC or whose pill counts reveal they took less than 50% of the reported optimized dose.   Safety analysis will be done on all patients who took at least one dose of the study medication.

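### Section 6.3 unblinds every participant who stops drug for an SAE, while Section 7.1 asks the same participants to go on completing the self-reported assessments used in the primary analysis

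*Protocol*

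**What the plan says.** Protocol Section 6.3 deals with code breaks in one paragraph. It opens with discretion: "Unblinding may be done in the case of some serious adverse events (SAEs"). It closes with an obligation: "In the event that a participant withdraws from the study or discontinues dronabinol due to a SAE, the participant will be unblinded". Nothing between the two says when the code is needed, who is to be told, or whether the participant and the assessors stay masked.

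Section 7.1 sets out what happens after drug is stopped. One sentence begins "In cases where a participant discontinues dronabinol for any reason, the Study" and goes on "Coordinator will ask the participant to continue to attend all study visits and complete assessments". SAE stops are therefore included. The same section lets monitoring after an SAE stop or withdrawal end when "the SAE is determined to be clearly unrelated to study intervention", and Section 8.3.3.2 has causality reassessed as information arrives.

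Section 3 names the PROMIS pain impact score, change from baseline to week 8, as the primary endpoint. The Schedule of Activities (Section 1.3) collects it at baseline, week 4 and week 8. On the analysis set, Section 9.3 states: "Primary analysis of all endpoints will be an intention to treat analysis".

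**The concern.** A self-reported pain score is the kind of endpoint that knowledge of the arm can move. A participant told that the capsules were placebo and one told that they were dronabinol may shift their later answers in opposite directions, and that difference enters the treatment comparison.

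The rule also runs against the care taken over masking elsewhere. The crossover design was given up because masking failed in its second period (Sections 2.2 and 4.2). Toxicology results are held back until the participant has finished, to protect the mask (Section 8.1). Section 6.1.1 concedes that participant blinding is imperfect. Disclosing the arm by rule while endpoint collection continues gives away something that the rest of the plan tries to keep.

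**Working it through.** The point is textual, so the first check is to follow one participant through the sections.

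1. An SAE occurs at week 3, is judged possibly related, and drug is stopped (Sections 6.3 and 7.1). This first relatedness call is made before the code is broken.
2. Because drug was stopped for an SAE, the last sentence of the Section 6.3 paragraph requires unblinding.
3. Section 7.1 asks the participant to keep attending. The week-4 and week-8 surveys (Section 1.3) follow.
4. Section 9.3 analyses by intention to treat, and no section sets these scores aside. The week-8 score enters the primary comparison.
5. Any later causality reassessment (Section 8.3.3.2), or a later decision that the event is clearly unrelated (Section 7.1), can be made with the arm known.

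How many participants take this path cannot be read from the plan. Criterion 7 in Section 7.1 lists SAEs as a reason to stop with no condition on relatedness: "7) serious adverse events, defined as those which result in death, are life threatening, require inpatient hospitalization or prolongation of existing hospitalization". Section 6.3 says the reverse for unrelated events: "Dronabinol will not be discontinued for SAEs determined to be unrelated to dronabinol, such as pain crisis". Section 8.3.2 takes hospitalization for uncomplicated pain crisis out of the SAE definition. These passages must be reconciled before the size of the unblinded group can be estimated.

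**The plan's own figure.** Section 9.2 uses a difference of 5 points, SD 6.5, two-sided 0.05 and 80% power, and states 28 per group. A two-sample t-test with these inputs needs 27.5, rounded up to 28, and has 80.7% power at 28. With 20% attrition, 56 / (1 − 0.20) = 70 enrolled. Both figures reproduce.

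**Scale, on assumed inputs.** Let k be the number in one arm of 28 who stop for an SAE, are unblinded and give a week-8 score. Let d be the average shift in their scores from knowing the arm. The documents give neither. The shift in the arm mean is k × d / 28.

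- k = 2, d = 3: 2 × 3 / 28 = 0.21 points
- k = 4, d = 5: 4 × 5 / 28 = 0.71 points

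A wider assumed range, k from 1 to 5 and d from 2 to 5, gives:

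- 1 × 2 / 28 = 0.07 points
- 5 × 5 / 28 = 0.89 points

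If that shift ran wholly against the treatment effect, t-test power at 28 per group would fall from 80.7% to 79.6% at the small end and 64.1% at the large end. The planned primary test is a rank-sum test (Section 9.4.2), which does not test a difference in means, so these figures indicate scale and are not predictions.

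**The case against.** The strongest reply is that the affected group is small and partly dealt with. Unrelated SAEs are exempt from stopping under one reading, and uncomplicated pain crises are not SAEs. Sections 9.3 and 9.4.1 also plan a secondary analysis that drops participants with under 4 weeks on study or under 50% of the optimized dose by pill count. A stop at week 3 is 3/8 = 37.5% of planned dosing, so that participant would be removed if the pill count is measured against the full 8 weeks. This stands in part. But a stop after week 5 (5/8 = 62.5%) would not be removed on dose, and the primary analysis keeps everyone.

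It can also be said that the closing sentence merely specifies which SAEs the opening one had in mind, and that being unblinded does not settle who is told. Both readings are possible. The text does not choose between them, and that is a reason to rewrite it.

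Four stronger readings are tempting, and the documents do not support them.

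- A reader might infer that participants who withdraw are also kept for the surveys. Section 7.1 asks this only of those who stop drug. Section 7.2 only encourages those with agent-related adverse events to stay in follow-up until resolution.
- A reader might detach withdrawal from the SAE condition and count all planned attrition as code breaks, 0.20 × 70 = 14. Section 7.1 uses the same clause and follows it with SAE monitoring only, so the condition most naturally covers both verbs. Those 14 are also non-completers, and the sample-size calculation does not count on a week-8 score from them.
- A reader might infer that a comparison of related events is biased. No such comparison is planned. Section 9.4.4 compares new adverse events and Section 9.4.6 serious ones, neither restricted to related events. The call that leads to stopping also comes before the code break.
- A reader might suppose that disclosure after stopping serves no clinical purpose. The protocol does not say so, and Section 2.3.1 describes symptoms on abrupt stopping.

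**Conclusion.** The concern holds for one group: participants who stop study drug because of an SAE and remain in follow-up. Followed as written, Sections 6.3, 7.1 and 9.3 allow their remaining self-reported scores, including the primary week-8 score, to be given with the arm known, and leave later causality reassessment open to the same. That follows from the text and needs no assumption about numbers.

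The size does rest on assumptions. With 2 to 4 of 28 in one arm and 3 to 5 points each, the shift is about 0.2 to 0.7 points against a target of 5. That is modest and would not by itself undermine the trial. It is also avoidable, so the change should be made.

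**What to change.** Rewrite the unblinding paragraph in Section 6.3 so that its two sentences agree with each other and with Section 7.1:

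- Replace automatic unblinding with code breaks decided case by case, keeping emergency unblinding available.
- Where the code is not broken, keep the participant and the outcome and causality assessors masked until the participant's week-8 assessments are complete or the trial is unblinded.
- Record relatedness before any code break, and log the date of each break and who was told.

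Separately, reconcile criterion 7 in Section 7.1 with the statements in Sections 6.3 and 7.1 on unrelated SAEs, since together they decide who reaches this rule. Which stopping rule is right is a clinical matter for the sponsor and the investigator.

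The cost is a few sentences and one log. The change leaves dosing, stopping rules and sample size as they are. The small downside is that some participants who stop learn their arm later.

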**Study Intervention Compliance**

**Measures of Adherence:** Blood toxicology and pill count results will be used to determine study drug adherence (both) and adherence to avoidance of other cannabinoid containing substances (blood only) and will be used during secondary non-intention to treat analysis of the data as described below.

**Pill Counts:**Patients should bring medication bottles to visits at weeks 2, 4 and 8.  Pills counts will be done at each visit and compared to pharmacy dispensing records.

**Blood measure of non-dronabinol cannabinoid use:**  Blood cannabinoids test will be done for multiple cannabinoids including THC, cannabidiol (CBD), and others.  This can distinguish 3 states: (1) recent dronabinol alone in which only THC will be present, (2) recent cannabis use, without or with dronabinol, in which multiple cannabinoids will be present and (3) no recent cannabis use in which no cannabinoids will be present.  This was shown to be able to distinguish dronabinol use from other illicit and medical cannabis use in our prior feasibility study.^69^  Blood will be collected at 4 weeks, and 8 weeks on study.

## 6.5 Concomitant Therapy

Subjects should continue all other medications, including pain medications, as used prior to enrolling in the study. All baseline medications, over the counter medications, herbals or supplements used will be collected at study enrollment.  As dronabinol may improve pain control resulting in subjects requiring less opioid use to treat pain, change in opioids used is a secondary endpoint.  Opioids will be reconciled with dispensing records from the New York Prescription Monitoring Program at baseline, week 4, and week 8. Opioids will be converted into OMEs. Patient’s own opioids will not be counted, only the study drug will be counted.

# 7 Study Intervention Discontinuation and Participant Discontinuation/Withdrawal

## 7.1 Discontinuation of Study Intervention

For serious adverse events (SAEs), defined as those which result in death, are life-threatening, require inpatient hospitalization or prolongation of existing hospitalization, result in significant disability or incapacity, or result in congenital anomaly or birth defect, [name] will be notified and if the event is determined to be possibly related to dronabinol it will be discontinued.  Dronabinol will not be discontinued for SAEs determined to be unrelated to dronabinol, such as pain crisis. In the event that a participant withdraws from the study or discontinues dronabinol due to a SAE, the participant’s ongoing status will be monitored by [name] until: 1) a resolution is reached, i.e., the problem requiring hospitalization has resolved or stabilized with no further changes anticipated; 2) the SAE is determined to be clearly unrelated to study intervention; or 3) the SAE results in death. In cases where a participant discontinues dronabinol for any reason, the Study

 Coordinator will ask the participant to continue to attend all study visits and complete assessments. Criteria for discontinuation of the randomization condition include 1) pregnancy; 2) current suicidal ideation with plan or intent; 3) suicide attempt; 4) severe anxiety episode, severe depression episode, or psychotic symptoms; 5) severe adverse events probably or definitely related to the randomization condition, as defined above; 6) adverse events that have the potential to cause serious impairment of health, including ischemic or arrhythmic adverse cardiovascular disease events (e.g., myocardial infarction, unstable angina, coronary revascularization, coronary artery disease, unstable arrhythmias, transient ischemic attack, stroke, or congestive heart failure); 7) serious adverse events, defined as those which result in death, are life threatening, require inpatient hospitalization or prolongation of existing hospitalization, result in significant disability or incapacity, or result in congenital anomaly or birth defect; or 8) the request of participants or their treating providers. [name] or the Study Coordinator will be responsible for informing the participant to discontinue the randomization condition and will ask the participant to continue to attend all study visits. Once the randomization condition has been discontinued it will be for the duration of the study.

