### 8.3.2 Definition of Serious Adverse Events (SAE)

An adverse event (AE) or suspected adverse reaction is considered "serious" if, in the view of the investigator, it results in any of the following outcomes:

- Results in death
- Is life-threatening (i.e., in the opinion of the investigator, the subject is at immediate risk of death from the AE)
- Requires inpatient hospitalization or prolongation of existing hospitalization (hospitalization is defined as an inpatient admission, regardless of length of stay)
- Results in persistent or significant disability/incapacity (a substantial disruption of the subject’s ability to conduct normal life functions)
- Is a congenital anomaly/birth defect
- Constitutes an important medical Important medical events are defined as those occurrences that may not be immediately life threatening or result in death, hospitalization, or disability, but may jeopardize the subject or require medical or surgical intervention to prevent one of the other outcomes listed above. Medical and scientific judgment should be exercised in deciding whether such an AE should be considered serious.

For this study, events not considered to be SAEs are hospitalizations for:

- Routine treatment or monitoring not associated with any deterioration in condition.
- The administration of blood or platelet transfusion as routine treatment of studied
- Emergency outpatient treatment or observation that does not result in admission, unless fulfilling other seriousness criteria
- Hospitalization for treatment of uncomplicated sickle cell pain crisis as defined by the investigator

If an AE is considered serious, both the AE eCRF and the SAE Report Form must be completed. For each SAE, the investigator will provide information on severity, start and stop dates, relationship to study agent, action taken regarding study agent, and outcome.

The principal investigator is responsible for reporting SAEs to the IRB and other applicable regulatory authority. The principal investigator is responsible for submitting follow-up reports for all SAEs regarding the patient’s subsequent course until the SAE has resolved or until the patient’s condition stabilizes (in the case of persistent impairment), or the death of the patient.

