#### 8.3.3.2 Relationship to Study Intervention

All adverse events (AEs) must have their relationship to study intervention assessed by the clinician who examines and evaluates the participant based on temporal relationship and his/her clinical judgment. The degree of certainty about causality will be graded using the categories below. In a clinical trial, the study product must always be suspect.

- Definitely Related – There is clear evidence to suggest a causal relationship, and other possible contributing factors can be ruled The clinical event, including an abnormal laboratory test result, occurs in a plausible time relationship to study intervention administration and cannot be explained by concurrent disease or other drugs or chemicals. The response to withdrawal of the study intervention (de-challenge) should be clinically plausible. The event must be pharmacologically or phenomenologically definitive, with use of a satisfactory re-challenge procedure if necessary.
- Probably Related – There is evidence to suggest a causal relationship, and the influence of other factors is The clinical event, including an abnormal laboratory test result, occurs within a reasonable time after administration of the study intervention, is unlikely to be attributed to concurrent disease or other drugs or chemicals, and follows a clinically reasonable response on withdrawal (de-challenge). Re-challenge information is not required to fulfill this definition.
- Potentially Related – There is some evidence to suggest a causal relationship (e.g., the event occurred within a reasonable time after administration of the trial medication). However, other factors may have contributed to the event (e.g., the participant’s clinical condition, other concomitant events). Although an AE may rate only as “possibly related” soon after discovery, it can be flagged as requiring more information and later be upgraded to “probably related” or “definitely related”, as
- Unlikely to be related – A clinical event, including an abnormal laboratory test result, whose temporal relationship to study intervention administration makes a causal relationship improbable (e.g., the event did not occur within a reasonable time after administration of the study intervention) and in which other drugs or chemicals or underlying disease provides plausible explanations (e.g., the participant’s clinical condition, other concomitant treatments).

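### Section 7.1 gives opposite instructions for a serious adverse event judged unrelated to study drug, and the choice decides both treatment and unblinding

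*Protocol*

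**What the plan says.** **Opening of Protocol 7.1, repeated in 6.3.** After an SAE, "if the event is determined to be possibly related to dronabinol it will be discontinued". The next sentence is the exemption: "Dronabinol will not be discontinued for SAEs determined to be unrelated to dronabinol, such as pain crisis". Section 8.3.5 repeats the exemption for events found not to be due to dronabinol, again with pain crisis as the example.

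**Criteria list later in 7.1.** Item 7 is "serious adverse events, defined as those which result in death, are life threatening, require inpatient hospitalization or prolongation of existing hospitalization", followed by disability and birth defect. It carries no relatedness condition. Item 5 of the same list does: "severe adverse events probably or definitely related to the randomization condition, as defined above". The paragraph closes: "Once the randomization condition has been discontinued it will be for the duration of the study".

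**Unblinding, 6.3.** "In the event that a participant withdraws from the study or discontinues dronabinol due to a SAE, the participant will be unblinded". The same paragraph opens more loosely, saying that unblinding is an option for some SAEs.

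**SAE definition, 8.3.2.** Among the events that are not SAEs in this study is "Hospitalization for treatment of uncomplicated sickle cell pain crisis as defined by the investigator". The definitions written out in 6.3 and 7.1 count any inpatient hospitalization and omit this exclusion.

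**Restart, 8.3.5.** Drug is stopped for all AEs of grade 3 or above and may be restarted once the event has resolved to a stated grade.

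**The concern.** Take a participant admitted for a reason that the investigator judges unrelated to study drug. Under the exemption, that person stays on drug and stays masked. Under criterion 7, the same person comes off drug for good and is then unblinded under 6.3. Two coordinators reading different paragraphs of one section could handle identical admissions in opposite ways.

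This matters more here than in many trials. The primary endpoint, change in PROMIS pain impact to week 8, is reported by the participant. Section 7.1 asks people who stop drug to keep attending visits and completing assessments, and 9.3 makes the primary analysis intention to treat. Week-8 scores from people who are off drug and know their arm would therefore enter the primary comparison. Masking is also a stated driver of the design: sections 2.2 and 4.2 say that the crossover was abandoned because all 6 pilot participants guessed their treatment correctly in the second phase. Hospital use is scheduled data in section 1.3, so admissions are anticipated.

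**Working it through.** The protocol states no figure on this point, so the check sets the rules side by side.

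| Event | Opening of 7.1, 6.3, 8.3.5 exemption | Criteria list in 7.1 | Agree? |
|---|---|---|---|
| SAE judged possibly related | Stop (7.1 opening, 6.3) | Stop (item 7) | Yes |
| Complicated crisis admission, judged unrelated | Continue | Stop for good (item 7) | No |
| Other SAE judged unrelated | Continue | Stop for good (item 7) | No |
| Uncomplicated crisis admission, judged unrelated | Continue | Not an SAE under 8.3.2; an SAE under item 7's own wording | Depends on the definition used |
| Infarction or stroke that is an SAE, judged unrelated | Continue | Stop for good (items 6 and 7) | No |

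**Step 1: can a relatedness condition be read into item 7?** Not safely. Item 5 states its condition in words and item 7 does not. Item 7 also repeats almost exactly the SAE definition that the opening of 7.1 uses, so the two rules cover the same events.

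**Step 2: is the list merely advisory?** It is introduced as criteria for discontinuation. The paragraph then makes named staff responsible for telling the participant to stop, and ends by making the stop permanent. No sentence ranks it below the opening of the section.

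**Step 3: does the choice reach masking?** Yes, through the 6.3 sentence on discontinuing due to an SAE. The permissive sentence earlier in that paragraph adds uncertainty about whether unblinding is automatic. It does not remove the later and firmer statement.

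**Step 4: permanence.** A grade 3 event judged probably related meets item 5, where the stop is final. The same event meets 8.3.5, where restart is allowed after resolution. Both cannot apply.

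**Step 5: how many participants?** The protocol gives no 8-week SAE or admission rate. For scale only, suppose that between 5% and 30% of the 70 enrolled had an admission or SAE on which the rules differ. Then 70 × 0.05 = 3.5 and 70 × 0.30 = 21 participants, both arms together. Those shares are assumptions with no source in the protocol, and the conclusion does not rest on them.

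**The case against.** The best defence is that the list should be read subject to the rule that opens its own section. For pain crisis every specific statement points the same way: 6.3, 7.1 and 8.3.5 say not to stop, and 8.3.2 says that an uncomplicated crisis admission is not an SAE at all. A sensible investigator would probably continue drug. This stands for the uncomplicated crisis, with one reservation: the definitions spelled out in 6.3 and 7.1 do not carry the 8.3.2 exclusion. It does not settle complicated crises or other unrelated SAEs.

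The contrast with item 5 should not be pressed too far either. Items 2, 3, 4 and 6, on suicidality, psychiatric episodes and cardiovascular events, also lack a relatedness condition, so relatedness is not the norm of the list. Some of these may be meant as safety stops whatever the cause, and the protocol should say so.

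Some readers might infer more than the text supports:

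- **That timing alone would bring a crisis under the stopping rule.** The Potentially Related grade in 8.3.3.2 begins "There is some evidence to suggest a causal relationship (e.g., the event occurred within a reasonable time after administration of the trial medication". Some evidence is required and timing is only an example. Lower grades are available for events that the underlying disease explains.
- **That several stopping triggers are a contradiction in themselves.** Severe and serious are different properties (8.3.3.1), so different rules can properly cover different events.
- **That the interim SAE comparison in 9.4.6 is undefined.** That section offers no competing definition, and 8.3.2 sets one for the study.
- **That follow-up after stopping is a flaw.** It is what intention to treat requires. The problem is the avoidable stopping and unmasking.

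**Conclusion.** The point holds as a contradiction in the current text. For an unrelated SAE, section 7.1 supports both continuing and stopping for good, and 6.3 attaches unblinding to the second. It is clearest for complicated crises and other unrelated SAEs, and weakest for the uncomplicated crisis. A second and separate conflict is that 7.1 makes every stop permanent while 8.3.5 permits restart.

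The size is unknown. A reader might infer a loss of power or a bias in a particular direction, for example if one arm had more admissions. The protocol gives no rates by arm or overall, so neither can be supported, and the section 9.2 sample size is not in question. The conclusion assumes only that staff may follow the criteria list as written. It is worth correcting because the rules govern participant safety and masking alike, and no other part of the protocol resolves them.

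**What to change.** 1. Limit criterion 7 to SAEs judged at least possibly related, defined as Potentially Related or higher in 8.3.3.2. State whether criterion 6 events stop drug regardless of relatedness, as a deliberate safety exception to the exemption.
2. Replace the SAE definitions written out in 6.3 and 7.1 by a reference to 8.3.2, so that the uncomplicated-crisis exclusion applies everywhere.
3. State once which stops are permanent under 7.1 and which may be restarted under 8.3.5.
4. Make the unblinding text in 6.3 consistent: one sentence, limited to SAEs for which drug is stopped under the corrected rule.

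The cost is a wording amendment to 6.3, 7.1 and 8.3.5. It needs no new data, visits or participants.
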